## Abstract

**Background:**

Despite the demonstrated need to increase screening mammography utilization and strong evidence that mail and telephone outreach to women can increase screening, most managed care organizations have not adopted comprehensive outreach programs. The uncertainty about optimum strategies and cost effectiveness have retarded widespread acceptance. While 70% of women report getting a mammogram within the prior 2 years, repeat mammography rates are less than 50%. This 5-year study is conducted though a Central Massachusetts healthcare plan and affiliated clinic. All womenhave adequate health insurance to cover the test.

**Methods/Design:**

This randomized study compares 3 arms: reminder letter alone; reminder letter plus reminder call; reminder letter plus a second reminder and booklet plus a counselor call. All calls provide women with the opportunity to schedule a mammogram in a reasonable time. The invention period will span 4 years and include repeat attempts. The counselor arm is designed to educate, motivate and counsel women in an effort to alleviate PCP burden.

All women who have been in the healthcare plan for 24 months and who have a current primary care provider (PCP) and who are aged 51-84 are randomized to 1 of 3 arms. Interventions are limited to women who become ≥18 months from a prior mammogram. Women and their physicians may opt out of the intervention study.

Measurement of completed mammograms will use plan billing records and clinic electronic records. The primary outcome is the proportion of women continuously enrolled for ≥24 months who have had ≥1 mammogram in the last 24 months. Secondary outcomes include the number of women who need repeat interventions. The cost effectiveness analysis will measure all costs from the provider perspective.

**Discussion:**

So far, 18,509 women aged 51-84 have been enrolled into our tracking database and were randomized into one of three arms. At baseline, 5,223 women were eligible for an intervention. We anticipate that the outcome will provide firm data about the maximal effectiveness as well as the cost effectiveness of the interventions both for increasing the mammography rate and the repeat mammography rate.

**Trial registration:**

http://clinicaltrials.gov/NCT01332032

## Background

Despite the demonstrated need to increase screening mammography utilization and the strong evidence that mail and telephone outreach to women can increase screening in the short term, most managed care organizations have not adopted comprehensive outreach programs for several reasons: 1) the continuing uncertainty about optimum outreach strategy, 2) the absence of practical and replicable models of such systems and 3) the lack of cost effectiveness data to guide decision-making. We undertook this study to compare three successful methods of promoting regular screening mammography (mailed reminders, reminder calls, and more intensive counseling calls) and to identify the most effective and most cost effective of these outreach strategies. Our findings should provide much needed and timely guidance for health plans [1] and Accountable Care Organizations (ACOs).

Determining the most effective way to reach women remains an urgent yet unfinished task. Although public health efforts have been promoting mammography for 25 years or more, national screening rates appear to have stalled. While 81% of American women, 50-74, report having a mammogram in the previous two years [2], only 46% woman get them *regularly *every 1-2 years [3]. A suboptimal level of screening is of considerable concern because the reduction in breast cancer mortality seen with screening mammography requires repeat mammography every several years [4,5]. Non-adherent women are at increased risk for developing advanced or non-curable breast cancers when compared to adherent women [6].

The three arms of the study are:

1) RL: A mailed reminder to schedule a mammogram. Mailed reminders have been shown to increase screening mammography rates by 25-50% [7-11] and have become usual care in some managed care organizations.

2) RC: A mailed reminder followed, if no response, by a reminder telephone call with facilitated access to mammography scheduling. Reminder calls have generally been more effective than reminder letters, especially when the former include the opportunity to schedule a mammogram [12,13]. It is important to confirm this finding in a large population of non-adherent women and especially in women long overdue for a mammogram.

3). ETTC: A mailed reminder followed, if no response, by a mailed educational booklet and, if still no response, by an enhanced tailored telephone counseling call (ETTC). Standard tailored telephone counseling (TTC) has been effective in a wide variety of health promotion outreach efforts [14-21] including efforts focused on cancer prevention and screening [22-25], breast cancer prevention [26] and breast cancer screening [27-33]. TTC has been most effective in breast cancer screening studies when it is used with women who have had a prior mammogram or a recent mammogram but less so in women who had never had a mammogram [27]. Overall, TTC interventions show an improvement in mammography completion rates over mailed reminders or mailed educational materials [13,34-37]. While TTC is often confined to tailored barriers [38], reluctant women may need more encouragement. We developed an enhanced TTC (ETTC) by adding techniques from motivational interviewing [39-43], informative print material and the ability to schedule mammogram on the call. We have pilot tested ETTC and it is effective in helping long overdue women schedule and complete screening mammograms [44,45].

### Study goals

The study goals are:

1) To compare the effectiveness of the three outreach interventions in increasing adherence to mammography screening guidelines in a large managed care population.

2) To identify ways to improve the efficiency and sequencing of the interventions by identifying patient factors and intervention mechanisms associated with increased intervention effectiveness through the evaluation of intermediate outcomes and sub-group analyses.

3) To determine the incremental cost-effectiveness of each telephone intervention compared to the reminder letter and of enhanced tailored telephone counseling to a reminder/scheduling call.

## Methods/design

### Study Design

#### Overall design

Figure 1 shows the overall design of the study. Beginning in July, 2009, all eligible women are automatically enrolled and randomized 1:1:1 to the three study arms. After approval by PCPs and passive consent, women are entered into the reminder study. The interventions (letters and calls) are directed only to women who have not had a mammogram in ≥ 18 months. The primary outcome is the proportion of all women who have been enrolled for ≥ 24 months with a mammogram within the previous 24 months. This outcome will be determined at five times, at baseline and at the end of each intervention year. Outcome at the end of the last intervention year will be the single most important result.

**Figure 1 F1:**
[figure not shown]
**Overview of study design**.

### Participants

All women aged 51-84 in the Fallon Community Health Plan (FCHP), for at least 24 months and have a primary care practitioner (PCP) at Fallon Clinic (FC) are eligible and are randomized to one of the three study arms. Exceptions are women with bilateral mastectomies, in hospice, in permanent nursing home care or those mentally incompetent. There are approximately 20,000 such eligible women ages enrolled in the plan at any given time. As women join the health plan or become 51, once in the plan for 24 months, they are enrolled and randomized into the study cohort. Enrollment into the reminder intervention study requires Primary Care Physician (PCP) approval and passive consent of the woman. PCPs are asked to exclude women using the exclusion criteria (See Table 1). Participants are given an opportunity to opt out of the study prior to being intervened, at the time of any intervention and during any phone call.

**Table 1 T1:** Eligibility Criteria

Inclusion Criteria	Exclusion Criteria
1. Age 51-84	1. History of bilateral mastectomies
2. Current patient of Fallon Clinic PCP	2. Significant cognitive impairment
3. Currently enrolled in FCHP	3. Serious illness, precluding screening
4. Has a working telephone	4. Life expectancy <5 years

### Study Setting

#### Study team

The team includes University of Massachusetts researchers (the study joint principal investigators, project manager, psychologist, health economist, biostatistician) and the Fallon Clinic researchers (the site manager, physician liaison, data analyst, schedulers and counselors). The study was approved by the Institutional Review Board for the Fallon Clinic/Fallon Community Health Plan Research Review Committee (IRB # 1191). The study will be conducted in compliance with the Helsinki Declaration.

#### Fallon Community Health Plan (FCHP) and Fallon Clinic Inc. (FC)

FC is a multi-specialty medical group located in Central Massachusetts with about 250 physicians and 20 medical centers. FC is the main group practice affiliated with FCHP, a mixed-model health maintenance organization (HMO) primarily serving the Central Massachusetts area. Automated tables in the FCHP "Data Warehouse" include in- and outpatient visits, laboratory tests and results, radiology procedures and membership. The FC maintains a centralized data repository with automatic feeds into the electronic record. Because most FC women get their mammograms at FC radiology sites, mammogram scheduled and completed dates are readily accessible. Completion data from non-FC sites are captured in billing and medical records. Although racial characteristics of FCHP members are not systematically captured, they reflect that of the Worcester Metropolitan area, which is about 90% White and 10% non-White.

#### Health Plan reminder activities include

An automated reminder call to women a few days before a scheduled mammogram appointment; an annual report to PCPs with the names of women failing to keep their mammogram appointments; at outpatient visits, PCPs receive a reminder in the electronic health record about overdue routine tests, including mammography status. PCPs are neither rewarded nor penalized for their responses.

#### Provider Responsibilities

109 of 111 FC PCPs agreed to: 1) participate in the study and 2) allow their patients to join the study, 3) review the list of their potentially eligible patients, 4) eliminate those having an exclusion criterion and 5) approve their electronic signature for personalized reminder letters. Two PCPs declined steps 3-5 and those functions were carried out by the FC study clinician.

### Interventions

Only women ≥ 18 months from a mammogram receive study interventions. See Figure 2. When women are ≥ 18 months from their last mammogram, they all receive the same reminder letter. The letter is electronically signed by a woman's PCP and states: 1) there is no record of a mammogram in the last 18 months, 2) getting regular mammograms every 1-2 years is important and 3) her PCP recommends that she call the Study Scheduler for a mammogram appointment. When women call, the Study Scheduler uses the same script for all, except as noted below for women in the counseling arm. (See Table 2 for Study Scheduler Protocol)

**Figure 2 F2:**
[figure not shown]
**Overview of Intervention Protocol Implementation**.

**Table 2 T2:** Study Scheduler Script for Incoming Calls

1. Confirm eligibility.
2. Obtain verbal consent for the baseline survey.
3. Stage the subject if the subject is unsure about scheduling, using Tables 3 and 4.
4. Schedule the mammogram. If the appointment is <= 24 months from the prior mammogram, reaffirm the importance of keeping on a 12-24 month interval schedule, and remind her to keep the appointment.
5. If a woman wants to schedule or confirm an appointment that is inappropriately far in the future, deliver a brief message reminding the woman that Fallon PCPs recommend mammograms every 12-24 months as the best way to find curable breast cancers. Offer to schedule at a more appropriate interval.
6. Administer the brief baseline survey questions that has 6 socio-demographic questions about ethnicity/race, educational level, working status, smoking, marital and income status.

#### RL Arm (reminder letter)

The reminder letter is the only intervention for women in this arm

#### RC Arm (reminder letter followed by Study Scheduler call)

All women receive a reminder letter as above. If a woman *does not call *following receipt of the reminder letter or does not schedule a mammogram on her own within two weeks of the reminder letter, the Study Scheduler makes up to five call-attempts to reach her. The script is the same as noted above.

#### ETTC Arm: (reminder letters and booklet followed by Counselor call)

All women receive a reminder letter as above. If a woman calls following receipt of the reminder letter, the Study Scheduler uses the same script as in Table 2 but replaces item #4 with "Inform the woman that she will receive a mammography booklet but will not get a Counselor call unless she would like to". If a woman calls in to schedule or confirm a mammogram appointment that is inappropriately far in the future, the Scheduler sends a mammography booklet and makes an appointment for her to receive a Counselor call.

If after receiving the reminder letter, a woman schedules a mammogram on her own, there is no further intervention. If a woman in the counseling arm does not call within two weeks after the first reminder letter, a mammography booklet is sent with a second reminder letter that states that if she does not call or schedule a mammogram within two weeks, a Counselor will call her. If the woman does not respond to the second reminder letter, the Counselor will make five call-attempts.

Counseling calls typically last about 30-35 minutes. If a subject requires a repeat counseling call during the study period, the call content will be different from that of the initial call. During repeat calls, the Counselor will address any change in the subject's stage of readiness, beliefs and barriers. The Counselor protocol using the CATI (computer assisted telephone interviewing) system was detailed in our previous publication [44,45].

Theoretical Basis of the Counseling Intervention:

1. Our counseling script incorporates a stage-based theory of behavior change that emphasizes the evolution of knowledge and personal risk perception in the development of an intention to act, and the variables that then influence acting on that intention [46,47]. The stage-based models have attempted to integrate the conceptual bases and empirical findings of the older models of change to capture the complexities of health behavior. The Precaution Adoption Process Model (PAPM) [48,49] is useful in working with non-adherent women because it classifies them into four stages that provide a more detailed description of the earlier stages of decision-making. In designing the ETTC counseling algorithm, we used our pilot mammography study to adapt the PAPM stages (See Tables 3 &4) [44,45].

**Table 3 T3:** Staging A Woman's Readiness to Get A Mammogram

STAGE	PAPM STAGES REVISED
1	Unaware - of mammography and guidelines

2	Unengaged - aware but does not see need to get mammogram

3	Undecided- considering the pros and cons of mammograms

4A	Definite No - would never get a mammogram

4B	Qualified No - but might reconsider

5A	Definite Yes - planning sometime

5B	Definite Yes - planning soon but cannot set date

5C	Definite Yes - planning soon and can set date

**Table 4 T4:** Initial Staging Questions

• For those with no record of a mammogram: "Have you ever had a mammogram"?
• If never had a mammogram: "Have you ever heard about a mammogram" "Do you know what a mammogram is?"
• For those who have had a mammogram: "Are you planning or thinking about getting a mammogram?"
• If planning: "Within 3 months?" "More than 3 months?" " Don't know when"
• If planning: "Can I schedule you now? When?"
• If not planning: "Have you decided not to get a mammogram?"
• If decided no: "Have you thought seriously about whether mammograms are for you?"
"Are you unable to decide to get a mammogram?" "Do you mean you would never get a mammogram or you would not get a mammogram unless something happened?"

2. The ETTC counseling algorithm interviewing and script use the following (MI) techniques [39]: 1) expressing empathy through reflective listening skills and a warm empathetic style; 2) developing discrepancy between the patient's current decision and future goals so that the patient verbalizes the need for screening; 3) avoiding argumentation; 4) "rolling with" resistance instead of arguing with it; 5) involving the patient in active problem solving; 6) supporting self-efficacy for screening change by facilitating the patient's own action plan for mammography completion.

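### As printed, the ETTC call-in script drops the step that books the mammogram, contradicting the protocol's statement that all calls offer scheduling, and ETTC callers left unbooked have no automatic follow-up

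*Protocol article*

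**What the plan says.** The Interventions section sends the same first letter to every woman 18 months or more from a mammogram. The letter tells her that "her PCP recommends that she call the Study Scheduler for a mammogram appointment". For the calls that follow, "the Study Scheduler uses the same script for all, except as noted below for women in the counseling arm".

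Table 2 is that script. Its fourth item reads "4. Schedule the mammogram. If the appointment is <= 24 months from the prior mammogram, reaffirm the importance of keeping on a 12-24 month interval", and it goes on to remind her to keep the appointment.

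The exception is in the ETTC Arm section. For a woman who phones after the first letter, "the Study Scheduler uses the same script as in Table 2 but replaces item #4 with" this text: "Inform the woman that she will receive a mammography booklet but will not get a Counselor call unless she would like to". The next sentence deals with ETTC callers whose date is too far ahead: they get a booklet and an appointment for a Counselor call.

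On escalation, the same section says: "If a woman in the counseling arm does not call within two weeks after the first reminder letter, a mammography booklet is sent", together with a second letter. The RC Arm section starts outbound call attempts when a woman has not called, or has not scheduled on her own, within two weeks.

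The Abstract (Methods/Design) states without an arm restriction: "All calls provide women with the opportunity to schedule a mammogram in a reasonable time".

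**The concern.** There are two separate problems.

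- **Booking step.** The first letter and the call it prompts are meant to be common to all arms. RL and RC callers reach item 4 and are booked. Under the printed wording, ETTC callers hear the booklet notice in its place. The women affected are the readiest ones: they have phoned, want a mammogram, and would accept a timely date.
- **Trigger.** An ETTC woman who has phoned but has no appointment does not meet the condition for the second letter, and so does not go on to the Counselor call that follows it. In RC, the scheduling condition covers the same woman.

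Study goals 1 and 3 compare the effectiveness and cost-effectiveness of the three sequences. If the script was followed literally, ETTC would differ from RC and RL by a lost booking step as well as by counseling. A smaller ETTC effect could then not be attributed to the counseling. The written script is also the standard against which taped calls are reviewed for fidelity, and it is what a health plan adopting the program would copy.

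**Working it through.** **1. Is a ready ETTC caller booked anywhere else in the script?**

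| Script element | Applies to | Booking for a ready caller wanting a timely date? |
|---|---|---|
| Table 2 items 1, 2 and 6 | all callers (eligibility, survey consent, survey) | no |
| Item 3, using Tables 3 and 4 | callers unsure about scheduling; Table 4 includes an offer to schedule now | no, she is not unsure |
| Item 4 | callers to be booked | yes, but replaced in ETTC |
| Item 5 | callers wanting a date too far ahead | no; ETTC has its own rule for these callers |
| ETTC replacement text | ETTC callers | no; booklet and optional Counselor call |

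Item 4 is the only element that covers her, and it is the one removed. That cannot stand beside the Abstract or the letter's invitation to phone for an appointment.

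**2. What follows a call that ends without an appointment?**

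| Caller left unbooked | RC | ETTC |
|---|---|---|
| Asks for a Counselor call | not applicable | Counselor call |
| Wants a date too far ahead | Table 2 item 5 | booklet and booked Counselor call |
| Any other reason | not scheduled within two weeks, so up to five call attempts | none stated; she has called, so the second-letter trigger is not met |

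The gap is the last row only.

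**3. The plan's own figure.** The Sample Size section states more than 99% power across groups with 5,000 per arm. The significance level is not given; I assume 0.05 two-sided. For the 2-df chi-square test, noncentrality = n × Σ(p − p̄)² / [p̄(1 − p̄)].

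- Scenario 1 (75/80/85%): 5,000 × 0.0050 / 0.16 = 156.
- Scenario 2 (80/83/86%): 5,000 × 0.0018 / 0.1411 = 63.8.

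Both give power above 99.9%, so the stated figure reproduces. For RC versus ETTC in scenario 2, SE = √(2 × 0.845 × 0.155 / 5,000) = 0.00724 and 0.03/0.00724 − 1.96 = 2.19, which gives 98.6%. This point disputes no power figure. The value is a reference for step 4.

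**4. Illustration of possible dilution.** Loss in the ETTC rate = f × c × u, where:

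- f = 5,223/18,509 = 28.2%, the share eligible for an intervention at baseline (Baseline results), taken as equal across arms;
- c = share of those women who phone after the first letter (assumed);
- u = share of those callers who miss a mammogram because no booking was made (assumed).

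| c | u | Loss (points) | ETTC rate, scenario 2 | Power vs RC at 83% |
|---|---|---|---|---|
| any | 0 | 0 | 86.0% | 98.6% |
| 10% | 10% | 0.3 | 85.7% | 96.3% |
| 20% | 25% | 1.4 | 84.6% | 58% |
| 30% | 50% | 4.2 | 81.8% | ETTC falls below RC |

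Check of the third row: 0.282 × 0.20 × 0.25 = 0.0141. The difference from RC is then 0.0159, SE = 0.00737, and 0.0159/0.00737 − 1.96 = 0.20, giving 58%. The documents give no value for c or u, so the table shows sensitivity and is not an estimate.

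**The case against.** A reader might infer more: that ETTC women who answer the first letter are neither booked nor escalated, and that the arm comparison is therefore biased against ETTC. The case against that reading is strong.

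- **Not booked.** The sentence after the replacement text concerns ETTC women who phone to schedule or confirm an appointment, so it presupposes that the Scheduler handles appointments in this arm. Items 3 and 5 also carry scheduling offers. Loose wording in a condensed article, with the notice meant as an addition, is at least as plausible as a script that withholds booking. This stands as an account of what may have been intended. It does not remove the contradiction, because the text gives an explicit replacement and items 3 and 5 do not reach the ready caller.
- **Not escalated.** This is too broad. A Counselor call is available on request and is arranged for callers with a far-off date. That second rule is a declared difference between arms and not a defect.
- **Biased.** The documents do not support this. Women are randomized and analyzed individually, so the trial validly compares the arms as delivered, whatever the script. What is at stake is what ETTC consists of, and nothing shows that the script was delivered literally.
- **Size.** Callers can still book on their own, and PCPs see overdue-test reminders at visits, so large values of u are not established and zero belongs in the range.

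The trigger gap does not depend on how item 4 is read. It remains for an unbooked caller even if item 4 was kept in practice.

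**Conclusion.** The point holds as an internal contradiction in an operative intervention rule. The ETTC Arm section, read with Table 2, leaves a ready caller without a booking step. The Abstract and the Interventions section say that calls offer scheduling. Separately, the ETTC and RC triggers differ, and an ETTC caller left unbooked for any reason other than a far-off date has no automatic follow-up unless she asks for a Counselor.

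The consequence is conditional. If the script was delivered as printed, the ETTC effect against RC and RL could be diluted by lost booking, and the cost-effectiveness contrasts would carry the same dilution. The loss is zero if callers were booked in practice. Otherwise it depends on two shares that the documents do not report. The assumed values above give 0.3 to 4.2 points, against a smallest planned difference of 3 points between adjacent arms, so it cannot be dismissed without data. It is not a finding of bias in the randomized comparison.

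**What to change.** 1. Reconcile the ETTC Arm section with Table 2, the Interventions section and the Abstract: state whether the booklet notice is added to item 4 or replaces it. If the Abstract's statement holds, it is an addition.
2. Reconcile the ETTC and RC triggers by stating what happens to an ETTC woman who phones but does not schedule within two weeks. If the existing rule is intended, say so.
3. If calls were already handled under the printed script, use the call logs and tracking database to count the ETTC callers who were not offered a booking and those left unbooked without follow-up. Report both numbers with the arm comparison.

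The first two items cost a few lines of text, plus a change to the Scheduler script or tracking trigger only if practice matched the print. The third uses the phone call logs and tracking data already listed in Table 5. No change to the sample size or to the primary analysis is needed.
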